# A double blind community-based randomized trial of amoxicillin versus placebo for fast breathing pneumonia in children aged 2-59 months in Karachi, Pakistan (RETAPP)

**DOI:** 10.1186/s12879-015-1334-9

**Published:** 2016-01-13

**Keywords:** Fast breathing pneumonia, Pneumonia, Integrated management of childhood illnesses, Amoxicillin, Placebo

## Abstract

**Background:**

Fast breathing pneumonia is characterized by tachypnoea in the absence of danger signs and is mostly viral in etiology. Current guidelines recommend antibiotic therapy for all children with fast breathing pneumonia in resource limited settings, presuming that most pneumonia is bacterial. High quality clinical trial evidence to challenge or support the continued use of antibiotics, as recommended by the World Health Organization is lacking.

**Methods/design:**

This is a randomized double blinded placebo-controlled non-inferiority trial using parallel assignment with 1:1 allocation ratio, to be conducted in low income squatter settlements of urban Karachi, Pakistan. Children 2–59 months old with fast breathing, without any WHO-defined danger signs and seeking care at the primary health care center are randomized to receive either three days of placebo or amoxicillin. From prior studies, a sample size of 2430 children is required over a period of 28 months. Primary outcome is the difference in cumulative treatment failure between the two groups, defined as a new clinical sign based on preset definitions indicating illness progression or mortality and confirmed by two independent primary health care physicians on day 0, 1, 2 or 3 of therapy. Secondary outcomes include relapse measured between days 5–14. Modified per protocol analysis comparing hazards of treatment failure with 95 % confidence intervals in the placebo arm with hazards in the amoxicillin arm will be done.

**Discussion:**

This study will provide evidence to support or refute the use of antibiotics for fast breathing pneumonia paving a way for guideline change.

**Trial registration:**

Clinical Trials (NIH) Register NCT02372461

## Background

World Health Organization (WHO)-defined pneumonia, a spectrum of clinical signs and symptoms varying from isolated fast breathing to presence of danger signs, is an important cause of child morbidity and mortality in low resource countries [1]. As a result, the WHO has recommended antibiotic prescription guidelines to cover the probability that most children with pneumonia-like symptoms have bacterial infections [2]. Recently, this broad recommendation for empiric antibiotic use in all children with pneumonia, including those with isolated fast breathing, has been questioned [3–7]. Furthermore, with the advent of *Haemophilus Influenza* type b (Hib) and pneumococcal vaccine in the Expanded Program of Immunization, there is protection against two most common bacterial pathogens of bacterial pneumonia. This has resulted in far smaller proportions of children with LRTI having a bacterial etiology and, as a corollary, more having benign viral infections [1, 8, 9]. In Pakistan for example, the Hib vaccine was introduced in the universal immunization program in 2009 and pneumococcal conjugate vaccine in 2013-14. Vaccine study for three doses of Hib has demonstrated the vaccine effectiveness in reduction of pneumonia from 62 %–70 % among Pakistani children [10], and pneumococcal vaccine studies are currently underway.

Children with ‘fast breathing pneumonia’ (previously classified by the WHO as “non-severe pneumonia”) relatively have mild illness, which in up to 65 % of cases is viral (8) with many of the remainder having self-limiting infection [11]. Spontaneous remissions are common and may render antibiotics redundant and potentially harmful. The risk of harm from unnecessary antibiotic use is twofold: individual and population level. At the individual level, side effects to antibiotics, both unpleasant and dangerous, must be considered. Frequent exposure to antibiotics has also been shown to have long-term deleterious effects on the native gut micro-biota that may impair growth and nutrition in children [12]. As a result of this, there may be altered immune processing resulting in long- term risk of subsequent infections [13–15]. At a public health population-based level, there is the risk of potential emergence of resistance of common pathogens to first line antibiotics and the need to use more expensive (sometimes more toxic) alternatives [16–18]. Infections due to antibiotic resistant pathogens not only make people ill for longer but also unnecessarily burden health care resources and increase cost [19].

The cost of antibiotic treatment for all children with WHO-defined pneumonia is formidable. An estimated US$ 200 million is the cost of antibiotic treatment for all children with pneumonia in South Asia & sub Saharan Africa [20]. In Pakistan, the average cost to treat one episode of pneumonia in a child as an outpatient was estimated to be US$ 13.44 in 2006, representing 82 % of annual health expenditure per person at that time [21]. Unnecessary antibiotic prescription is a major contributor to antibiotic resistance and puts a strain on individuals and under-resourced program in low-income countries. This crisis has arisen largely as a result of increased antibiotic use with the predictable consequence of microbial mutation to the point that, in some settings, many previously pan-susceptible organisms are now almost untreatable. The problem is particularly acute in South Asia. A recent systematic review of etiology in developing countries of infant sepsis aged 1–12 months with no clear focus of infection in developing countries has shown in vitro susceptibility to chloramphenicol/penicillin, penicillin/gentamicin, and third-generation cephalosporin of only 47 %, 63 %, and 64 %, respectively [22].

The last comprehensive Cochrane review looking at use of antibiotics in pneumonia conducted up to 2009 showed that among 27 studies, comparing multiple antibiotics, none were found to compare antibiotic with placebo [23]. Another Cochrane review done last year which looked at antibiotic versus no antibiotic therapy in children with non-severe pneumonia and wheeze did not find a single study meeting inclusion criteria and concluded that there is a lack of evidence and randomized controlled trials are needed to address this question in representative population [24]. Two recent randomized controlled trials (RCTs) compared placebo to amoxicillin for the management of non-severe pneumonia, now called fast breathing pneumonia. Hazir et al [5] conducted a double-blinded, RCT of oral amoxicillin versus placebo for non-severe pneumonia in four centers in Pakistan, using age-dependent WHO cut-offs for dosing. Cumulative treatment failure (TF) by day 3, defined as appearance of any danger sign or onset of lower chest indrawing, was similar in both groups: 7.2 % (31/431) of children in the amoxicillin group and 8.3 % (37/442) in the placebo group. Between the arms there was no statistically significant difference in relapse by day 14, the number of children requiring change (or initiation) of antibiotics, the number of children who developed danger signs, or the number of children requiring hospitalization. There were no deaths. The second randomized placebo controlled multi-centre trial was conducted in India in out-patient clinics associated with tertiary care hospitals [4]. This trial used the WHO criteria for non-severe pneumonia, but only enrolled children with wheeze (audible or auscultatory). TF rates at day 4 was defined as development of WHO-defined severe or very severe pneumonia, hypoxaemia (SpO_2_ < 90 %), fever (temperature >101^0^ F) or persistence of non-severe pneumonia, or wheeze. TF among placebo recipients was 24.0 % (201/836), while among the amoxicillin group it was 19.9 % (166/835). The rate difference was 4.2 % (95 % CI 0.2 to 8.2); however, there was no difference in the rates of relapse. Clinical failure due to the development of severe or very severe pneumonia or hypoxemia was similar between groups. These trials were conducted before Hib and pneumococcal vaccines were introduced in the local setting.

In summary, there is equipoise regarding utility of antibiotics for mild lower respiratory tract illnesses (LRTI). In children 2 to 59 months of age there is no high quality trial evidence in managing children with fast breathing pneumonia in community settings and the WHO has called for evidence on which to update guidelines [25]. Our proposed trial is comparing standard antibiotic treatment with placebo for children 2 to 59 months of age in poor urban slum settings in Karachi, Pakistan where pneumococcal or Hib vaccine has been previously implemented.

### Hypothesis

The null hypothesis for this trial is that the absolute treatment failure rate of children 2–59 months of age presenting at a primary healthcare (PHC) facility for treatment of WHO defined fast breathing pneumonia who receive 3 days of placebo is worse than 3 days of amoxicillin by 2.5 % (TF_placebo_—TF_amoxicillin_ > 2.5 %, assuming TF of 5 % in amoxicillin group).

The alternate hypothesis is that absolute treatment failure rate of children 2–59 months of age presenting at a primary healthcare (PHC) facility for treatment of WHO defined fast breathing pneumonia who receive 3 days of placebo is equal to or not worse than 3 days of amoxicillin by 2.5 % (TF_placebo_—TF_amoxicillin_ ≤ 2.5 % assuming TF of 5 % in amoxicillin group).

### Research question

The primary research question is to assess among children 2 to 59 months of age with WHO-defined fast breathing pneumonia presenting at a PHC facility, if treatment with 3 days of placebo is non-inferior to three days of oral amoxicillin (reference therapy). The secondary research question is to evaluate the proportion of children with fast breathing pneumonia who have pneumococcal carriage, viral carriage or both in nasopharyngeal specimens and to evaluate predictors of treatment failure (TF) with regards to viral or bacterial nasopharyngeal carriage.

## Methods

### Design

This is a randomized double blinded placebo-controlled non-inferiority trial with parallel assignment and treatment allocation ratio of 1:1.

### Patients

#### Setting

The study is currently being carried out at four primary healthcare centers (PHC) located in low-income communities in peri-urban areas of Karachi (Fig. 1). The Department of Paediatrics and Child Health, AKU has maintained health and demographic surveillance in these areas since 2003. As of 2010 baseline census, the total population is 198,494, total children under 5 are 28,005, under-5 mortality is 76/1000 live births, HIV sero-prevalence is <0.1 % among pregnant women, and malaria endemicity is low at these sites.

**Fig. 1 Fig1:**
[figure not shown]
Map of Karachi and RETAPP study sites (inset). Source: Data Management Unit, Department of Pediatrics and Child Health Aga Khan University

#### Inclusion and exclusion criteria

Children 2–59 months old, visiting primary health clinics (PHC) run by Aga Khan University (AKU) with following eligibility criteria are included (Table 1).

**Table 1 Tab1:** Eligibility Criteria

Inclusion	Exclusion
Children 2–59 months old who are visiting PHC History of cough or difficult breathing less than 14 days^a^ (observed or reported) Respiratory rate ≥ 50 breaths per minute in children 2 to <12 months OR respiratory rate ≥ 40 breaths per minute in children ≥12 months^b^ Providing written informed consent	Antibiotics taken in last 48 h Lower chest wall in-drawing Any general danger sign as defined by WHO *(Stridor when calm, hypoxia defined as SaO* _*2*_ *< 90 % in air, inability to feed, persistent vomiting, convulsions or reduced conscious level)* Bulging fontanel Pedal edema Known asthmatics, tuberculosis or other severe illness History of hospitalization in last two weeks Congenital heart disease Any surgical condition requiring hospitalization Out of catchment area Enrolled in another trial or previously enrolled in study

^a^Children, who present with wheeze along with cough or difficulty in breathing, are given trial of nebulization with bronchodilator up to three times 15–20 min apart. These children are then re-assessed for respiratory rate after each nebulization therapy. If respiratory rate remains persistently above cut-off, irrespective of wheeze, child is considered for inclusion. For persistent wheezers, oral bronchodilator is given for three days

^b^On two consecutive readings by community health worker and physicians

### Intervention

Children in the reference arm receive the WHO regimen of oral Amoxicillin in two divided doses for three days using WHO Integrated Management of Childhood Illnesses (IMCI) recommended weight bands [26] (Table 2). Children in the comparison arm receive pharmacologically inert placebo similar in appearance in two divided doses for three days.

**Table 2 Tab2:** WHO age and weight bands and drug doses

Age (Weight)	Amoxicillin Dose^a^ (250/5 ml) (Morning & Evening)
2 months up to 12 months (4-˂10 kg)	5 ml
12 months up to 3 years (10- ˂14 kg)	10 ml
3 years up to 5 years (14 – ˂ 20 kg)	15 ml

^a^Or an equal amount of placebo

### Recruitment and follow-up

Children between 2 to 59 months old with cough or difficult breathing, presenting at the participating PHCs are screened for eligibility by the study physicians. If eligible the parent/guardian is referred to an independent physician to obtain written informed consent. If consent is given and child is enrolled then randomization serial identification number will be assigned. All enrolled children will receive study drug by CHW in accordance with the randomization number in morning and evening on day 0, 1 and 2.

Children are followed for compliance and outcome twice daily on days 0, 1, 2, 3, with a morning assessment by a study physician in the study clinic and a home visit in the evening by a CHW. Subsequently, children are seen by a study physician once on days 5, 14 and 21. At follow-up visits participants will be examined by study physician in the morning and CHW in the evening for resolution of high respiratory rate along with signs of treatment failure and relapse (Fig. 2). All adverse events are recorded on the adverse event reporting form (AERF). The schedule of follow-up is derived from our experience of a trial in younger infants [27] and taking into consideration safety of the enrolled children.

**Fig. 2 Fig2:**
[figure not shown]
Flow of participants in the study

### Blinding and randomization

The randomization technique is stratified block randomization with varying sized blocks of 4, 6, 8 and 10 to prevent prediction of next assignment and to ensure sequence allocation concealment. Random sequence lists are stratified by age group (2–11 months and 12–59 months) to maintain similar composition of ages in both study arms. Separate randomization lists stratified by age (‘IN’ for infants 2–12 months of age and ‘CH’ for children 12–59 months of age) with drug labels (antibiotic or placebo) will be generated. This is done to reduce the chance that prescription errors will occur as investigators are using different weight bands for antibiotic dosages in these two age groups. Sequence generation was done at the AKU Clinical Trials Unit (CTU), electronically via computer using random selection method before the start of the study. This was done by an independent person unrelated to the trial.

This is a blinded study in which the drug assignment will be concealed from patients, parents, and study personnel. To ensure blinding, self-adhesive, pre-coded sticking labels with the unique identification numbers are prepared at the CTU and applied to the opaque medication bottles before providing to the study physicians. 4 digit randomization codes are used with two prefix characters for different age groups (e.g. IN0000, CH0000). Differentiation in code by age is to minimize chances of error in prescribing the wrong bottle. The codes will be kept safe with a person completely unrelated with the trial and broken only after analysis or upon the recommendation of the DSMB. This will ensure blinding of both the allocating physician as well as the one performing outcome assessment. Moreover, medication will be dispensed by community health workers who are not involved in treatment allocation and outcome assessment.

### Sample size

In the study of Hazir et al [28], cumulative TF rates at day 3 were reported to be between 4 % and 7 % in tertiary level hospital setting. Given that the currently described study is conducted in a primary care setting, investigators have estimated that the TF rate of 5 %. Assuming a TF rate of 5 % in both the arms, using one sided alpha of 0.05, power of 85 %, non-inferiority margin of 2.5 % and an expected 10 % lost to follow-up/non per protocol, the minimum total estimated sample size required is 2430. Placebo will be judged to be “no worse” than amoxicillin if the lower bound of the 95 % confidence interval lies in the allowed margin.

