### Statistical analysis

Baseline characteristics will be compared by analyzing differences in means and proportions among the study arms using the *chi-square* test for proportions and Student’s *t*-test for continuous variables. The primary analysis of outcomes will be a modified per protocol analysis comparing hazards of treatment failure with 95 % confidence intervals in the placebo arm with hazards in the amoxicillin arm. In order for an enrolled child to be included in the modified per protocol analysis, s/he must have received 5 out of 6 doses, including 4 doses in the first two days. Adjusted hazard rate ratios will be estimated accounting for the effect of any baseline variable found to differ between the two arms. Intention to treat analysis will also be performed for comparison.

Additionally, analyses will be done to identify predictors of treatment failure. Baseline characteristics between cumulative treatment success and failure groups by day 3 will be compared using the *chi square* test for categorical variables and Student’s *t*-test for continuous variables. A multivariate model will be constructed to look for determinants of cumulative treatment failure at day 3. All analysis will be done using STATA version 12. Sub-group analyses will be performed by age category, nasopharyngeal carriage, wheezing and initial fever.

Investigators propose to conduct one interim analysis using the O’Brien Fleming rule when 50 % per protocol subject accrual has been achieved. Termination will be done if p < 0.01 is observed with respect to the null hypothesis of inferiority. Final analysis will be done once enrollment is complete.

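### The sample size uses a one-sided alpha of 0.05, but non-inferiority is judged by a 95% confidence interval; under that rule 2430 children give about 76% power, not 85%

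*Protocol article*

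**What the plan says.** All the design inputs are in the Sample size section of the protocol article:

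- Failure rates: "Assuming a TF rate of 5 % in both the arms".
- Error rate and power: "using one sided alpha of 0.05, power of" 85%.
- Margin: "non-inferiority margin of 2.5" percentage points. It is an absolute difference, because the null hypothesis in the Hypothesis section is that 3 days of placebo "is worse than 3 days of amoxicillin by 2.5" points.
- Loss: "an expected 10 % lost to follow-up/non per protocol".
- Result: a minimum total of 2430.

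The closing sentence of that section is the success criterion. Placebo is accepted if the lower bound of the 95% "confidence interval lies in the allowed margin".

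The Statistical analysis section describes the primary modified per protocol analysis as a comparison of hazards with 95% "confidence intervals in the placebo arm with hazards in the amoxicillin arm". The Abstract repeats this. The article nowhere calls the interval one-sided and nowhere mentions a 90% interval.

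**The concern.** A one-sided test at 5% corresponds to one limit of a two-sided 90% interval. One limit of a two-sided 95% interval corresponds to a one-sided test at 2.5%. The Sample size section uses the first to obtain 2430 and then, read conventionally, applies the second to judge success. On that reading the stated alpha, interval level and power do not fit together.

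Two things are at stake. If the 95% interval governs, the trial has less power than it claims. If the one-sided 5% test governs, the reported 95% interval is not the decision interval. Between the two lies a band of results for which the text supports either verdict. The Conclusion section says a finding of non-inferiority may make the case for changing treatment guidelines, so the rule should not be open to choice once the data are known.

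**Working it through.** **Inputs** (Sample size section, with 1:1 allocation from the Design section): failure rate p = 0.05 in both arms, so the true difference is 0; margin 0.025; power 0.85; loss 10%; total N = 2430, or 1215 per arm.

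**Formula.** Evaluable children per arm:

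n = (z₁₋α + z₀.₈₅)² × 2p(1 − p) / margin²

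Here 2p(1 − p) = 2 × 0.05 × 0.95 = 0.095, margin² = 0.000625 and z₀.₈₅ = 1.0364.

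**Step 1: reproduce the plan's figure (one-sided alpha 0.05).**
n = (1.6449 + 1.0364)² × 0.095 / 0.000625 = 1092.8, so 1093 per arm.
Allowing for loss: 1093 / 0.9 = 1214.4, so 1215 per arm and **2430** in total. This matches the protocol exactly.

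**Step 2: same inputs at one-sided 0.025 (one limit of a two-sided 95% interval).**
n = (1.9600 + 1.0364)² × 0.095 / 0.000625 = 1364.7, so 1365 per arm.
Allowing for loss: 1365 / 0.9 = 1516.7, so 1517 per arm and **3034** in total.

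**Step 3: power of the planned 2430 under each rule.**
Power = Φ(margin / SE − z₁₋α), with SE = √(0.095 / n).
After 10% loss, n = 1215 × 0.9 = 1093.5, SE = 0.00932 and margin / SE = 2.682.

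- 90% interval: Φ(2.682 − 1.645) = 85.0%
- 95% interval: Φ(2.682 − 1.960) = 76.5%

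**Step 4: sensitivity to the loss and the method.**

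| Share evaluable | Evaluable per arm | Power, 90% interval | Power, 95% interval |
|---|---|---|---|
| 90% (as planned) | 1093.5 | 85.0% | 76.5% |
| 95% | 1154 | 86.7% | 78.7% |
| 100% | 1215 | 88.1% | 80.7% |

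With the Farrington-Manning variance and 90% evaluable, the figures are 84.1% and 75.0%. No row reaches 85% under the 95% interval.

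**Step 5: results that could be called either way.** As an illustration, take 1093 evaluable per arm and 55 amoxicillin failures (5.0%), with simple Wald limits for placebo minus amoxicillin.

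| Placebo failures | Difference (points) | 90% upper limit | 95% upper limit |
|---|---|---|---|
| 61 | 0.55 | 2.13 | 2.43 |
| 62 | 0.64 | 2.22 | 2.53 |
| 63 | 0.73 | 2.32 | 2.63 |
| 64 | 0.82 | 2.42 | 2.73 |
| 65 | 0.91 | 2.52 | 2.82 |

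With 62, 63 or 64 placebo failures, placebo is non-inferior by the 90% interval and not by the 95% interval. Outside that band the two rules agree.

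**The case against.** The strongest reply is that a one-sided 95% confidence bound was meant. The sentence before the criterion names a one-sided alpha of 0.05, the criterion refers to a single bound, and the hypotheses run in one direction. On that reading everything agrees and power is 85%. The possibility is real, and it means the power shortfall depends on reading the interval as two-sided. But the article does not say so. An unqualified 95% confidence interval is ordinarily two-sided, and every two-sided interval has a lower bound. The criterion is also a poor guide to an unstated convention, because it names the lower bound although the Hypothesis section defines the difference as placebo minus amoxicillin, for which the upper bound must be compared with +2.5 points. Even if a one-sided bound was intended, the text has to say it.

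Other points on that side:

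- The sample-size arithmetic itself is correct. This stands: the fault is the mismatch between the test used for sizing and the rule used for the decision.
- The hazard comparison in the Statistical analysis section states no margin and no decision rule, so it is only supporting evidence. This also stands. The case rests on the two sentences in the Sample size section.
- Loss may be below 10%. The Limitations and bias section cites compliance above 93% and a 95% benchmark. That narrows the shortfall but does not close it, as Step 4 shows.
- A 95% interval errs on the cautious side. This is true of the type I error, but the stated power is then wrong.
- The full protocol or analysis plan may settle the matter. It may, but this is not an omission: the article states alpha, power, sample size and interval level, and read in the usual way they conflict.

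**Conclusion.** The concern holds. The sample size was computed for a one-sided 5% test, while the stated success criterion, read in the usual way, is a one-sided 2.5% test. Against that criterion, 2430 children with the planned 10% loss give about 76.5% power (75.0% by Farrington-Manning), roughly 8.5 points below the stated 85%. The risk of missing true non-inferiority is about 23.5% instead of 15%.

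These figures assume a two-sided 95% interval, 5% failure in both arms and analysis on the risk-difference scale of the Hypothesis and Sample size sections. They ignore any alpha used at the planned interim analysis. If a one-sided 95% bound was intended, power is as stated, and the defect is that the decision interval is not identified. Either way the primary success criterion must be corrected or clarified.

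**What to change.** Choose one of the following before unblinding and make every statement agree with it.

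1. **Keep the two-sided 95% interval.** Restate the design as one-sided alpha 0.025 with about 76% power at a total of 2430. This needs no more patients and holds a guideline-relevant claim to the stricter error rate. The cost is a less favourable stated power.
2. **Keep one-sided alpha 0.05.** State that the decision uses a two-sided 90% interval, equivalently a one-sided 95% bound, and correct the success criterion in the Sample size section. In the Statistical analysis section and the Abstract, either change the 95% level or say that those intervals are descriptive and do not decide non-inferiority. Power stays at 85%. The cost is openly accepting a 5% one-sided error.

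Either choice is a change of wording only. Keeping both the 95% interval and 85% power would instead mean about 3034 children, 604 more than planned (3034 − 2430).

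When the criterion is rewritten, it should also say that the upper limit of placebo minus amoxicillin failure is compared with +2.5 percentage points.

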### Outcomes

The primary outcome will be cumulative treatment failure at or before day 3 (Table 3). Secondary outcome includes treatment adherence, new onset infectious co-morbidity, severe and non-severe adverse event, relapse, pneumococcal and viral carriage and cost of treatment.

**Table 3 Tab3:** Treatment failure criteria^a^

Criterion	Days of assessment						
	0	1	2	3	5	14	21
Death	Treatment failure				Relapse		Vital status check
Any danger sign^b^							
Onset of lower chest in drawing							
Hospitalization due to any reason							
Change of antibiotic by study physician for new onset comorbidity or serious non-fatal antibiotic associated adverse event							

^a^Chest X-ray, blood for culture is processed for all treatment failures and relapses

^b^Unconscious/lethargy, convulsions, unable to feed, stridor when calm, hypoxia (paO2 < 90 %) in air, vomits everything

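### The final non-inferiority criterion names the lower confidence bound, but on the protocol's own contrast (failure on placebo minus failure on amoxicillin) the upper bound must decide

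*Protocol article*

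**What the plan says.** **Contrast.** The Hypothesis section of the protocol article sets the null as "TF_placebo_—TF_amoxicillin_ > 2.5 %, assuming TF of 5 % in amoxicillin group" and the alternative as "TF_placebo_—TF_amoxicillin_ ≤ 2.5 % assuming TF of 5 % in amoxicillin group". In words, the null is that failure in children "who receive 3 days of placebo is worse than 3 days of amoxicillin by" 2.5 points.

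**Outcome.** Under Outcomes: "The primary outcome will be cumulative treatment failure at or before day 3". Failure is an unfavourable event, so larger values of placebo minus amoxicillin mean more harm from placebo.

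**Analysis.** The Statistical analysis section compares hazards of failure with 95% "confidence intervals in the placebo arm with hazards in the amoxicillin arm". This too is placebo relative to amoxicillin, with harm on the high side.

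**Decision rule.** The last sentence of Sample size judges placebo no worse "than amoxicillin if the lower bound of the" 95% confidence interval falls inside the permitted margin.

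**Design.** The same section gives the planning values: "Assuming a TF rate of 5 % in both the arms", one-sided alpha 0.05, power 85%, margin 2.5%, 10% lost or not per protocol, total 2430.

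**The concern.** To reject a null of the form placebo minus amoxicillin above +2.5, the whole plausible range of the difference must lie below +2.5. That is a condition on the upper bound. A lower bound below +2.5 shows only that the data have not proved an excess larger than the margin. That condition can be met while placebo is clearly worse, and it is met more easily as the interval widens.

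The Conclusion section says that a finding of non-inferiority may support changing treatment guidelines. The rule that licenses that finding should agree with the hypothesis it tests, and it should be settled before unblinding so that nobody has to choose the bound once results are known.

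**Working it through.** **1. Reproduce the sample size.** With 5% failure in both arms, margin 0.025, z(0.95) = 1.645 and z(0.85) = 1.036:

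n per arm = (1.645 + 1.036)² × 2 × 0.05 × 0.95 / 0.025² = 7.189 × 0.095 / 0.000625 = 1092.8, rounded up to 1093.

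1093 / 0.90 = 1214.4, rounded up to 1215 per arm, so 2430 in total. This matches exactly. The sample size therefore assumes the correctly directed test at one-sided 0.05.

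**2. Chance of passing under each rule.** Assume 1093 evaluable per arm, 5% failure on amoxicillin, a true excess d on placebo and an unpooled Wald interval:

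- SE = √[0.05 × 0.95/1093 + p(1 − p)/1093], with p = 0.05 + d.
- Literal rule, read as lower bound ≤ +2.5 points: P = Φ((0.025 − d)/SE + z).
- Upper-bound rule: P = Φ((0.025 − d)/SE − z).
- z is 1.645 for a one-sided 95% bound and 1.960 for a two-sided 95% interval.

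| True excess d | SE (points) | Literal rule, one-sided 95% | Literal rule, two-sided 95% | Upper bound, one-sided 95% | Upper bound, two-sided 95% |
|---|---|---|---|---|---|
| 2.5 points | 1.034 | 95% | 97.5% | 5% | 2.5% |
| 4.0 points | 1.088 | 60% | 72% | 0.12% | 0.04% |
| 5.0 points | 1.122 | 28% | 39% | <0.01% | <0.01% |

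One million simulated trials at the margin gave 97.6% for the literal rule with the two-sided interval. For the upper-bound rule they gave 2.6% (two-sided 95%) and 5.1% (one-sided 95%).

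**3. Largest observed excess that passes.** Solve d − z·SE = 0.025 for the literal rule and d + z·SE = 0.025 for the upper-bound rule.

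- One-sided 95%: 4.3 points (literal) against 0.9 (upper bound).
- Two-sided 95%: 4.7 points (literal) against 0.6 (upper bound).

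As an illustration with the two-sided interval, take 106/1093 (9.7%) failures on placebo and 55/1093 (5.0%) on amoxicillin. The difference is 4.67 points and SE is 1.113, so the interval runs from 2.48 to 6.85. Placebo is plainly worse, yet the lower bound is under 2.5 and the literal rule passes it.

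**4. Other readings of lying in the margin** (two-sided 95% interval, true excess 2.5 points).

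- Lower bound between −2.5 and +2.5: 97.3%.
- Lower bound above −2.5: 99.8%.
- Lower bound between 0 and +2.5: 65%. This reading passes truly equal arms only 2.5% of the time, so it cannot be what is meant.

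None comes near the planned 5%.

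**5. Power of the corrected rule with equal arms.** SE = √(2 × 0.05 × 0.95/1093) = 0.932 points, and 2.5/0.932 = 2.68.

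- One-sided 95% bound: Φ(2.68 − 1.645) = 85.0%.
- Two-sided 95% interval: Φ(2.68 − 1.960) = 76.5%.

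**The case against.** The strongest reply is that this is a slip of wording. The hypotheses point the right way, the sample size reproduces from the correct test, and the interim rule in Statistical analysis is framed against a null of inferiority. All of that stands. A reader might infer that the trial was designed with a false-positive rate near 97.5%, or that 2430 is wrong. The documents support neither. A reader might also take this sentence as the only success rule of any kind, but the interim rule is a second one and is correctly directed.

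A second reply is that the sentence names no contrast. For amoxicillin minus placebo failure against −2.5, or for placebo minus amoxicillin success, the lower bound would be right. That is true in principle, but the article never states a reversed contrast, a success scale or a negative margin. The contrast it does state makes the lower bound the wrong one.

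Third, the size depends on the confidence level and on how the sentence is read. That is why both levels are shown; 97.5% alone would be the more extreme choice.

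Finally, the figures cannot be carried over to the hazard comparison. Harm is on the high side there as well, but the only margin given is an absolute 2.5 points, so no error rate for a hazard-ratio rule can be derived.

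An unseen analysis plan does not remove the point. The rule is stated here and stated wrongly, so a correct analysis plan would contradict this article.

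**Conclusion.** The point holds as a contradiction between one sentence in Sample size and the Hypothesis section. It concerns the only criterion the article states for the final conclusion, so it must be corrected, although the design around it is sound. Taken literally, the sentence passes placebo about 95% to 97.5% of the time at a true excess equal to the margin, against a planned 5%, and 28% to 39% of the time at twice the margin.

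These figures rest on the risk-difference scale, 1093 evaluable children per arm, 5% failure on amoxicillin, a normal approximation, and reading the sentence as lower bound at or below +2.5 points.

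**What to change.** Replace the last sentence of Sample size with:

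> Placebo is non-inferior if the upper one-sided 95% confidence bound (the upper limit of the two-sided 90% confidence interval) for TF(placebo) minus TF(amoxicillin) at day 3 is below +2.5 percentage points.

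The level has to be named, because moving to the upper bound without it leaves the rule undetermined. The wording above matches the planned one-sided alpha of 0.05 and 85% power. If the two-sided 95% interval is kept instead, restate one-sided alpha as 0.025 and power as about 76.5% at this sample size.

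The cost is one sentence in the protocol, with the same wording in the analysis plan, made before unblinding. With the one-sided 95% bound, enrolment, sample size and trial conduct do not change.
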